## Abstract

**Background:**

Metabolic disease is increasingly impacting women of reproductive age. In pregnancy, uncontrolled metabolic disease can result in offspring with major congenital anomalies, preterm birth, and abnormal fetal growth. Pregnancy also accelerates the complications of metabolic diseases in mothers resulting in an increased risk of premature cardiovascular events. Despite the convincing evidence that preconception care can largely mitigate the risks of metabolic disease in pregnancy, there are few data about how to identify the highest-risk women so that they can be connected with appropriate preconception care services.

**Objective:**

The aim of the study is to determine the maternal phenotype that represents the highest risk of having adverse neonatal and maternal pregnancy outcomes.

**Methods:**

This will be a prospective cohort study of 500 women recruited in early pregnancy. The primary outcome is a composite of offspring born small for gestational age (SGA) or large for gestational age (LGA) (customized birthweight ≤10th and ≥90th centile for gestational age). Secondary outcomes are (1) composite of adverse neonatal birth outcomes (SGA, LGA, major congenital abnormalities, preterm birth [<37 weeks’ gestation]) and (2) composite of new maternal metabolic outcomes (gestational diabetes, diabetes in pregnancy, type 2 diabetes [T2D] or prediabetes; gestational hypertension, preeclampsia, eclampsia or new essential hypertension after pregnancy; and gestational weight gain ≥20kg or new overweight/obesity at the 12-18 months postpartum visit). A multivariable logistic regression analysis will be conducted to identify candidate predictors of poor pregnancy outcomes due to metabolic disease. From this model, model coefficients and the associated 95% CIs will be extracted to derive the risk score for predicting the delivery of LGA/SGA offspring (primary outcome) and composites of adverse neonatal outcomes and maternal outcomes (secondary outcomes).

**Results:**

Seed funding for the project was acquired in November 2022 and subsequent funding was acquired in May 2024. The first participant was recruited on March 23, 2023. At the time of manuscript submission, 402 participants have been recruited. Data analysis has not yet been performed. Results are expected to be published in the first half of 2027.

**Conclusions:**

This is a prospective observational cohort study that intends to identify the metabolic disease risk factors, or combination of factors, that are most likely to cause adverse maternal and fetal health outcomes. These characteristics will be used to develop a risk calculator which will assist in identifying the highest risk women and in triaging them to appropriate services. The study has been approved by the institutional Human Research Ethics Committee (HREC/90080/MH-2022).

**Trial Registration:**

Australian New Zealand Clinical Trials Registry ACTRN12623000037606; https://tinyurl.com/yeytsxtp

**International Registered Report Identifier (IRRID):**

DERR1-10.2196/72542

## Introduction

The offspring of mothers with pre-existing metabolic diseases—obesity, diabetes, and hypertension—have an increased risk of significant congenital anomalies and premature birth compared with the offspring of mothers without metabolic disease [1]. These offspring are also twice as likely to develop obesity, diabetes, and hypertension in childhood [2]. For the mothers, pregnancy accelerates the complications of metabolic diseases, resulting in an increased risk of premature cardiovascular events including ischemic heart disease, stroke, and death [3]. Although the consequences of uncontrolled metabolic disease in pregnancy are entirely preventable, our current clinical services are not effective. This is because the highest-risk women are often not identified prior to pregnancy and because high-risk women frequently have poor access to appropriate care.

The women who are most at risk of adverse consequences of metabolic disease in pregnancy are women of low socioeconomic status, women who have experienced trauma, and women living in rural and remote areas [4]. Major barriers for these women accessing and using preconception services include (1) failure to be identified as “high risk” by a health care provider prior to pregnancy; (2) accessing a suitable referral pathway; (3) attending clinic appointments especially if limited by remoteness or finances; and (4) accepting care for metabolic diseases which are often stigmatized diseases and may have implications for the women’s place in her family or wider cultural group. Ironically, there are well-developed services for preconception care of women with severe metabolic disease. However, these services are generally based in tertiary maternity hospitals in metropolitan cities. Due to geographical factors and because referral pathways and clinic entry criteria are often unclear, these services are often used by high socioeconomic status women with a relatively low risk of adverse pregnancy outcomes.

We hypothesize that the mothers and offspring at the highest risk of the adverse consequences of metabolic disease are predictable based on the phenotype of the mother prior to pregnancy. Despite the high fetal morbidity that can be associated with metabolic syndrome, little has been done to identify and capture at-risk individuals at a preconception or early antenatal stage. The aim of this study is to develop risk calculators that best predict (1) a mother’s risk of having a neonate with abnormal fetal growth (large for gestational age [LGA] or small for gestational age [SGA]); (2) a mother’s risk of having a serious adverse neonatal outcome; and (3) a mother’s risk of developing new metabolic disease after pregnancy (Figure 1). We will translate this to a user-friendly mobile app that will allow any health care worker to access and triage women to appropriate preconception care.

**Figure 1 figure1:**
[figure not shown]
Schematic of the rationale for research study.

## Methods

### Study Design and Setting

Study phase I is a multicenter prospective observational cohort study. Study phase II involves the development of risk calculators from the observational cohort established in phase I. The study was prospectively registered with the Australian New Zealand Clinical Trials Registry (ACTRN12623000037606).

The observational cohort study will recruit 500 women who have been referred to either a public or a private tertiary maternity hospital (Figure 2). Both hospitals are tertiary referral centers based in metropolitan Melbourne Australia, and collectively manage >8000 births per year. The recruiting maternity hospitals accept referrals from the entire state of Victoria, such that the hospital populations comprise of metropolitan women and a smaller group of women living in regional and rural areas.

The first participant was recruited on March 23, 2023. The projected timeline for recruitment is that the last participant will be recruited in June 2025. It is anticipated that the last participant will have completed all study visits by June 2026.

**Figure 2 figure2:**
[figure not shown]
Flowchart of the anticipated study cohort.

### Eligibility and Recruitment

#### Inclusion Criteria

Eligibility for the study will be women aged 18 years and older with pregnancies of 20±4 completed weeks of gestation who provide written consent and are attending a prespecified study site for maternity care. The study will include those with multifetal pregnancies, chronic disease, and those using medications of any type. Women from non–English speaking backgrounds will be included and telephone interpreting services and cultural liaison officers will be used as required.

#### Exclusion Criteria

Women will be excluded from the study if they do not have maternity care at one of the prespecified study sites before 20±4 completed weeks of gestation. Women will also be excluded if they do not wish to provide informed consent or are unable to provide informed consent. This may be due to the inability to read and write, intellectual disability, or a severe active mental illness. It is anticipated that fewer than 1 out of 1000 women screened at maternity hospitals would fulfill this criterion.

#### Withdrawal Criteria

Participants are free to withdraw from the study at any time through revocation of consent (patient preference) or via ceased communication with the recruitment site (lost to follow-up). All data collected prior to the withdrawal of consent will be included in the analysis. Participants who start with maternity care at the recruiting hospitals and then move to seek maternity care elsewhere may continue to take part via telephone/telehealth study visits. Participants who have a pregnancy or neonatal loss will not continue in the study, but information collected until this point will be included in the analysis.

### Recruitment Procedure

Women will be recruited when they attend maternity care visits between 16 and 24 weeks’ gestation. Initial contact will be made by the maternity care provider. Subsequent contact will be made by a dedicated study nurse/doctor at the time of the standard maternity care visit. All participants will receive standard individualized antenatal care based on their clinical needs.

No study activities will be performed before eligibility has been assessed and informed consent has been formally documented. To encourage attendance at clinical visits, parking and meal vouchers will be provided. At the final visit, women will be provided with a comprehensive summary of their metabolic health and a plan for appropriate long-term follow-up.

### Expected Outcomes

#### Primary Outcomes

Metabolically prone offspring defined as a composite of offspring with birthweight ≥90th centile (LGA) and offspring with birthweight ≤10th centile (SGA) based on population-based charts [5,6].

#### Secondary Outcomes

A composite of adverse neonatal outcomes includes the following:

Offspring with birthweight ≥90th centile on population-based charts (LGA).Offspring with birthweight ≤10th centile on population-based charts (SGA).Offspring with major congenital abnormalities.Offspring born preterm (<37 completed weeks’ gestation).

A composite of new maternal metabolic disease that develops during pregnancy or <18 months postpartum is defined below:

Gestational diabetes (GDM) as per the International Association of the Diabetes and Pregnancy Study Group (IADPSG)/World Health Organization (WHO) definition (reference); or diabetes in pregnancy as per WHO/IADPSG definition; or previously undiagnosed type 2 diabetes as per American Diabetes Association/WHO definition; or prediabetes as per American Diabetes Association definition (Table S1 in Multimedia Appendix 1).Gestational hypertension; or pre-eclampsia; or eclampsia; or new essential hypertension after pregnancy (Table S2 in Multimedia Appendix 1).Gestational weight gain ≥20 kg or new overweight/obesity after pregnancy (BMI ≥25 kg/m^2^ and body weight increase of ≥5 kg compared with prepregnancy weight) at the 12-18 months postpartum visit.

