#### Oral Glucose Tolerance Test Results and Other Forms of Testing for Gestational Diabetes

The 75-g oral glucose tolerance test (OGTT) is a standard of care to screen for GDM at 24-28 weeks’ gestation in Australia. A 75-g OGTT may also be performed at 10-20 weeks of gestation if there are risk factors for GDM. A diagnosis of GDM may also be made using other methods such as HbA_1c_ (hemoglobin A_1c_), glucose readings from a period of fingerstick monitoring, or by evaluating continuous glucose monitoring CGM) metrics. If the woman is considered to have GDM by the treating clinical team, she will also be given this diagnosis for the purpose of the study. All medications used to treat GDM will be recorded.

For all such women, a 75-g OGTT or some other form of testing for diabetes should be repeated >6 weeks’ post partum and these results will also be collected.

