### Statistical Methods

This study will follow the Transparent Reporting of a Multivariable Prediction Model for Individual Prognosis or Diagnosis reporting guidelines for prognostic studies [14]. Summary characteristics of the study cohort will be described using means (with SD) or medians (with IQRs) for continuous variables, depending on the shape of the distribution, and numbers and percentages for categorical variables.

A risk calculator will be developed to determine the risk of an abnormally grown fetus (ie, the primary outcome of the study). Participant data will be split randomly into either training (70%) or validation (30%) datasets according to standard prediction model methods. Multivariable logistic regression analysis will be conducted to identify candidate predictors of poor pregnancy outcomes due to metabolic disease. After starting with the most comprehensive model that includes all potential risk factors for an LGA or SGA offspring (ie, the primary outcome). These include categorical variables including maternal SES (based on postcode), maternal parity, maternal smoking status, maternal obesity class, maternal preexisting diabetes, maternal preexisting renal disease, essential hypertension, use of antihypertensive medication, use of metformin, gestational hypertension, preeclampsia/eclampsia, previous LGA/SGA offspring, major congenital anomaly, and continuous variables including maternal age, maternal gestational weight gain, maternal glycemic control (HbA_1c_), total daily dose insulin, maternal systolic blood pressure, maternal diastolic blood pressure, birthweight of previous offspring, fasting glucose, plasma insulin, plasma C-peptide, plasma leptin, HOMA-IR.

A backward selection method will be performed to determine which combination of risk factors generates the most parsimonious predictive model. The number of candidate variables will be limited to data collected in the dataset. From this parsimonious model, model coefficients and the associated 95% CIs will be extracted to derive the risk score for predicting the delivery of LGA/SGA offspring. Internal validation of the model will be performed using 5-fold cross-validation and bootstrap validation. The performance of the model will be assessed using the AUC and calibration slope.

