A similar approach will be taken for the secondary outcomes, and these models will be used to develop risk calculators for a composite of neonatal adverse outcomes and a composite of maternal adverse outcomes. Ongoing statistical input will be provided by the University of Melbourne.

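### The maternal composite is called new disease, but existing overweight can count as new, gestational diabetes has two rules, and no at-risk set is defined for women already ill

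*Protocol article*

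**What the plan says.** All references are to the protocol article.

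- **Outcome (Secondary Outcomes).** The maternal endpoint is "A composite of new maternal metabolic disease that develops during pregnancy or <18 months postpartum is defined below". It has a diabetes domain, a hypertension domain and a weight domain. The diabetes domain covers gestational diabetes by the IADPSG/WHO definition, diabetes in pregnancy, prediabetes, "or previously undiagnosed type 2 diabetes as per American Diabetes Association/WHO definition". The hypertension domain lists pre-eclampsia and eclampsia with no condition on baseline blood pressure. The weight domain includes "new overweight/obesity after pregnancy (BMI ≥25 kg/m^2^ and body weight increase of ≥5 kg compared with prepregnancy weight").
- **Gestational diabetes (section on glucose tolerance testing).** HbA1c, fingerstick readings and continuous monitoring are accepted as routes to the diagnosis, and "If the woman is considered to have GDM by the treating clinical team, she will also be given this diagnosis".
- **Population (Inclusion Criteria).** "The study will include those with multifetal pregnancies, chronic disease, and those using medications of any type".
- **Predictors (Statistical Methods).** The candidate list for the primary outcome contains "maternal obesity class, maternal preexisting diabetes, maternal preexisting renal disease, essential hypertension, use of antihypertensive medication", and also metformin use, insulin dose, HbA1c and fasting glucose. For the other endpoints, "A similar approach will be taken for the secondary outcomes, and these models will be used to develop risk calculators".
- **Expected rates (Sample Size).** About 15% diabetes, 15% hypertensive disease and 5% excessive weight gain, giving about 20% (n=90) with at least one. The denominator is women in general, not women free of disease at baseline.

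**The concern.** A model for incident disease needs an outcome that only incident cases can meet and a denominator of women who could become cases. The stated rules fall short in three separate ways.

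(a) The overweight rule puts no condition on BMI before pregnancy. A woman who was already overweight or obese and is 5 kg heavier at the late visit is labelled new. Because the rule is easier to meet from a higher starting BMI, it builds an association with obesity class into the outcome.

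(b) The two rules for gestational diabetes can classify the same woman differently, in a domain that the plan expects to supply 15 of every 100 women.

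(c) A woman with known diabetes cannot newly acquire diabetes. A woman with essential hypertension cannot develop gestational or new essential hypertension. If these conditions, or their treatments, are predictors in a full-cohort maternal model, their coefficients mix real risk with the closure of one route to the outcome. The study wants to identify exactly these women as high risk, so a downward pull on their predicted risk would work against the calculator's purpose.

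**Working it through.** **Inputs.** Component rates d = 0.15 (diabetes), h = 0.15 (hypertensive disease), w = 0.05 (excessive gain), composite c = 0.20 and analysable N = 475, all from Sample Size. The prevalence of pre-existing diabetes or hypertension is not stated; I assume 2% to 20%. Height for the BMI illustration is assumed to be 1.65 m (height squared 2.7225).

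**Step 1: the plan's own figure.** 0.20 × 475 = 95 and 0.20 × 500 = 100, whereas the plan gives about 90. That figure is 90/475 = 18.9%, or 20% of an unstated 450. The gap is small, sits behind an approximation sign, and does not affect this point.

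**Step 2: is a 20% composite compatible with the components?** The union lies between max(d, h, w) = 15% and d + h + w = 35%. Under independence it is 1 − 0.85 × 0.85 × 0.95 = 31.4%. So 20% is possible but implies strong overlap, as the plan itself says.

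**Step 3: losing the diabetes component.** What remains is the union of hypertension and weight. It is at least 15% (weight cases all inside hypertension) and at most 20% (no overlap, 0.15 + 0.05). Against a woman open to all three routes at 20%:

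- remaining 15%: OR = (0.15/0.85)/(0.20/0.80) = 0.176/0.250 = 0.71
- remaining 20%: OR = 0.250/0.250 = 1.00

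This assumes the same risk of the other components in both groups. The artefact is cancelled once the risk of the remaining components in women with diabetes is 0.20/0.20 = 1.00 to 0.20/0.15 = 1.33 times that of other women.

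**Step 4: essential hypertension.** Removing the whole 15% hypertension domain would give the same 0.71 to 1.00. As worded, pre-eclampsia and eclampsia stay open to these women, so the loss is only partial and the artefact is no larger than that.

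**Step 5: the overweight rule.**

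- Prepregnancy BMI 32: weight 32 × 2.7225 = 87.1 kg; adding 5 kg gives 92.1/2.7225 = 33.8. She meets the rule although obesity was already present.
- Prepregnancy BMI 20: reaching BMI 25 takes 5 × 2.7225 = 13.6 kg.
- A 5 kg gain is enough from BMI 25 − 5/2.7225 = 23.2 upwards.

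**Step 6: the gestational diabetes rules side by side.** Secondary Outcomes fixes a named criterion. The testing section gives the study diagnosis to anyone the clinical team regards as having the condition, by several methods. A woman diagnosed on fingerstick readings alone is a case under the second rule and need not be one under the first. The article does not say which prevails.

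**Step 7: cost of restricting to baseline-free women.** With 2% to 20% excluded, N = 475 × 0.98 = 466 down to 475 × 0.80 = 380. Events at 20% fall to 93 down to 76.

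**The case against.** A reader might infer that women with diabetes or hypertension are scored as non-events. The article does not say so. A woman with diabetes can be an event through hypertensive disease or weight. A woman with essential hypertension can be one through gestational diabetes, weight and, as worded, pre-eclampsia or eclampsia.

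A reader might also infer that pre-existing disease will look protective, citing the independence calculation: 19.25% against 31.4%, an odds ratio of 0.52. The plan's 20% composite rules that scenario out. The Discussion also expects women with metabolic disease to be at higher risk, so their remaining-component risk may well outweigh the artefact. Nor do the other two parts point towards protection: the overweight rule pushes obesity upwards, and the gestational diabetes conflict has no set direction.

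The predictor list is written for the primary outcome. It cannot transfer unchanged, because it contains gestational hypertension, pre-eclampsia and gestational weight gain, which are themselves parts of the maternal composite. An at-risk set could be in an analysis plan not shown, and the appendix tables of definitions, also not shown, might narrow the diabetes and hypertension components. That makes (c) the least certain part.

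The overweight rule does require a 5 kg gain, so static overweight is not counted. Glucose tolerance testing at 24 to 28 weeks is described as the standard screen, so dependence of ascertainment on risk factors is limited to the additional early testing.

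What stands: the overweight wording and the two gestational diabetes rules are on the face of the text. For (c), the article enrols women with chronic disease, names the outcome new, and carries a similar approach over without naming who is at risk.

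**Conclusion.** The concern holds in this limited form. The overweight component labels some existing overweight or obesity as new. Gestational diabetes has two unreconciled outcome rules. The maternal model has no stated at-risk set although part of the composite is closed to some enrolled women.

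For known diabetes, the structural effect is an odds ratio of 0.71 to 1.00. It is nil only in the extreme case where every woman with new diabetes also has another component. This rests on the plan's component rates applying to women open to all three routes, on equal background risk, and on pre-existing diabetes being carried into the maternal model. The weight rate in the plan covers excessive gestational gain only, so the late overweight component is not in the calculation.

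The coefficient is pulled downwards, but its final sign cannot be determined from the documents. The size of (a) and (b) cannot be estimated without the number of women affected. The point concerns a secondary outcome, but the rules decide who counts as an event and feed a planned calculator.

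**What to change.** The article reports that no analysis has been done, so the following can be settled beforehand.

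1. **Overweight.** Require that the woman was below the relevant BMI class before pregnancy, or keep the rule and rename the component as postpartum weight gain or retention with BMI of 25 or more.
2. **Gestational diabetes.** Reconcile the two sections into one outcome classification, and flag women who meet only the other rule for a sensitivity analysis. This concerns outcome coding only, not care. Women diagnosed without a glucose tolerance test need a stated coding rule.
3. **At-risk set.** Define component-specific at-risk sets, or add a sensitivity analysis in women free of diabetes and essential hypertension at baseline. Do not interpret coefficients for pre-existing disease or its treatment (insulin dose, metformin, antihypertensives) in a full-cohort maternal model as risk effects. Excluding all such women from the main model is not advised, because it would discard valid events such as pre-eclampsia.

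Cost: wording changes and no new data, since prepregnancy weight is already needed for the outcome and glucose tolerance results are already collected. The maternal model loses some events. The baseline-free analysis would have about 93 to 76 events in 466 to 380 women under the assumed 2% to 20% prevalence.

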### Clinical Assessments

A schedule of assessments and measurements is presented in Table 1.

**Table 1 table1:** Summary of study activities.

	Visit 1 (20, SD 4 weeks gestation)	Visit 2 (36, SD 4 weeks gestation)	Visit 3 (Peripartum)	Visit 4 (12-18 months postpartum)
Informed consent and eligibility	✓	✓		
Collect basic demographic details including postcode	✓			
Collect past medical, surgical, obstetric, and gynecological	✓			
Collect new medical, surgical, obstetric, and gynecological		✓	✓	✓
Adverse events		✓	✓	✓
Medication	✓	✓	✓	✓
Allergies	✓	✓	✓	✓
Smoking, drug, and alcohol use history	✓			
Maternal Anthropometry				
Height	✓			
Weight	✓	✓		✓
Waist circumference	✓	✓		✓
Bioimpedance	✓	✓		✓
Blood tests				
Glucose, insulin, and c-peptide	✓	✓		✓
HbA_1c_^a^	✓	✓		✓
CRP^b^	✓	✓		✓
Leptin	✓	✓		✓
Provide maternal and neonatal mouth swabs to participants		✓		
Collect 75g OGTT^c^ result		✓		✓
Collect obstetric ultrasound results		✓		
Collect maternal and neonatal mouth swabs for epigenetic analysis		✓	✓	
Collect obstetric medical records including the birth summary		✓	✓	
Collect height and weight data from the childhood development book (“Baby book”)		✓		✓

^a^HbA_1c_: hemoglobin A_1c_.

^b^CRP: C-reactive protein.

^c^OGTT: oral glucose tolerance test.

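### The postpartum overweight/obesity component can be met by the weight of a new pregnancy at Visit 4, so some normal second pregnancies can count as new maternal metabolic disease

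*Protocol article*

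**What the plan says.** The Secondary Outcomes section introduces the maternal composite with "A composite of new maternal metabolic disease that develops during pregnancy or <18 months postpartum is defined below". Its third component is met either by a large gestational weight gain or by "new overweight/obesity after pregnancy (BMI ≥25 kg/m^2^ and body weight increase of ≥5 kg compared with prepregnancy weight) at the 12-18 months postpartum visit". The rule is complete in itself: it sets two thresholds, a comparator weight and a time point.

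Table 1 under Clinical Assessments has weight measured at Visit 4. It also ticks Visit 4 for the row "Collect new medical, surgical, obstetric, and gynecological", so a new pregnancy should be on record by then.

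No passage links the two. Withdrawal Criteria covers revoked consent, loss to follow-up, and one pregnancy-related case: "Participants who have a pregnancy or neonatal loss will not continue in the study". A subsequent pregnancy is not mentioned there, in the eligibility criteria or in the outcome definition.

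**The concern.** The component is meant to capture weight that was retained or newly gained after the index pregnancy. A weight taken during or shortly after another pregnancy also contains gestational weight, and the rule does not separate the two. Where gestational weight takes a woman over both thresholds, a normal second pregnancy is scored as new metabolic disease.

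The maternal risk calculator is to be built on this composite. False events would raise the apparent event rate. If early re-conception is related to maternal age or parity, both of which Statistical Methods lists as candidate predictors, the misclassification would be differential. The model would then partly learn who conceives again soon. That link is plausible, but the article gives no data on it.

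**Working it through.** **1. The planned event count.** Sample Size anticipates that about 20% of women (n=90) will have at least one maternal outcome, and expects 475 women after dropout.

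- 0.20 × 475 = 95
- 0.20 × 450 = 90
- 90 / 475 = 18.9%

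So 90 is not exactly 20% of 475. The point does not rest on this difference: 90 is used below as the planned count and 95 as 20% of 475. The weight element named in that forecast is excessive gain of more than 20 kg (about 5%). Postpartum overweight is not listed, so events from it, true or false, are not visibly budgeted.

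**2. Who can meet the rule through gestational weight.** Let g be the gain in kg over the weight before the index pregnancy, and h the height in metres. Both conditions must hold: g ≥ 5, and prepregnancy BMI + g/h² ≥ 25. The lowest qualifying prepregnancy BMI is therefore 25 − g/h². At h = 1.65, h² = 2.7225:

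| Gain g (kg) | g/h² | Lowest qualifying prepregnancy BMI |
|---|---|---|
| under 5 | – | never qualifies |
| 5 | 1.84 | 23.2 |
| 10 | 3.67 | 21.3 |
| 12 | 4.41 | 20.6 |

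A woman who starts at BMI 20 does not qualify even after gaining 12 kg. One who starts at 22 qualifies at 10 kg but not at 8 kg. One who starts at 24 qualifies at 5 kg. False events are thus possible but not automatic: they depend on starting BMI, height and the stage of the new pregnancy.

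**3. How many.** The article gives none of the following, so they are assumptions:

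- q, the share pregnant again or recently delivered at Visit 4: 2% to 15%
- m, the share of these who meet the rule only because of gestational weight: 20% to 80%
- the share of those not already cases through another component: 80%

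False events = 475 × q × m × 0.8.

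| q | m = 20% | m = 50% | m = 80% |
|---|---|---|---|
| 2% | 1.5 | 3.8 | 6.1 |
| 5% | 3.8 | 9.5 | 15.2 |
| 10% | 7.6 | 19.0 | 30.4 |
| 15% | 11.4 | 28.5 | 45.6 |

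With 95 true cases, the composite proportion would move from 20% to (95 + 1.5)/475 = 20.3% at the low end and (95 + 45.6)/475 = 29.6% at the high end. The calculation also assumes that all 475 women have a usable Visit 4 weight.

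**The case against.** The strongest reply is that this is silence, not error. The source is a condensed article, and scoring women who are pregnant at a follow-up visit could be left to the full protocol or analysis plan. An assessor might also read the words about overweight after pregnancy as excluding a current pregnancy. Visit 4 already collects new obstetric history, so the women can be found at analysis, and only one component of one secondary composite is touched.

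Much of this stands, and it limits the point to a modest one. It does not remove it. The article states a full scoring rule, and that rule, followed literally, gives the wrong answer for these women. In context, the postpartum wording refers to the index pregnancy.

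Stronger readings are tempting but not supported:

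- **Every woman pregnant again becomes an event.** Step 2 of the working shows otherwise. Some women will also have kept 5 kg or more before conceiving again; those who also met the BMI threshold by then are true events.
- **A firm large share of events is false.** Assuming 5-15% pregnant again (24-71 women) and half of them meeting the rule gives 12-36 events, or 13-40% of 90. Both inputs lack support in the article, and women who are already cases are not deducted.
- **Second-pregnancy gestational diabetes or preeclampsia is wrongly credited to the index pregnancy.** The window wording is open to that reading, but this is an ambiguity, not a demonstrated error. Such disease would also be real disease in the mother.
- **Women will be enrolled twice.** Recruitment opened in March 2023 and "The projected timeline for recruitment is that the last participant will be recruited in June 2025", and eligibility refers to "women aged 18 years and older with pregnancies of 20±4 completed weeks of gestation" without an explicit one-pregnancy rule. But the cohort is defined as 500 women, so the unit is the woman, and nothing shows double counting.

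**Conclusion.** The point holds in a limited form. The overweight/obesity rule can be met through gestational weight by some women who are pregnant again or recently delivered at Visit 4, and the plan does not prevent their being counted as events.

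The size is unknown because the article gives no repeat-pregnancy rate. Under the assumed ranges it is about 1.5 to 46 false events against roughly 90 planned, from negligible to about half of that count (45.6/90 = 51%). The mid-range cells with m = 50% and q = 5% or 10% give 9.5 to 19, or 11% to 21% of 90. The maternal calculator is affected; the primary outcome (small or large for gestational age) and the neonatal composite are not. Correction is worthwhile because it is cheap and, according to Results, no data analysis had been done when the article was submitted.

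**What to change.** Use the obstetric history already collected at Visit 4 to identify women who are pregnant again or have recently delivered again. Add to the outcome definition that, for these women, the postpartum weight component is scored from the last available weight before the new conception and, where there is none, is set to missing, not to event.

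In the same place, state that the pregnancy-specific components (gestational diabetes, gestational hypertension, preeclampsia) refer to the index pregnancy. This settles the ambiguity in the window.

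The cost is a short addition to the definition and the date of any new conception, if the obstetric history does not already record it. The downside is some missing postpartum weight values, which the analysis of the maternal composite will have to handle.
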